## Abstract

**Background:**

Achieving a shift from car use to walking, cycling and public transport in cities is a crucial part of healthier, more environmentally sustainable human habitats. Creating supportive active travel environments is an important precursor to this shift. The longevity of urban infrastructure necessitates retrofitting existing suburban neighbourhoods. Previous studies of the effects of street changes have generally relied on natural experiments, have included few outcomes, and have seldom attempted to understand the equity impacts of such interventions.

**Methods:**

In this paper we describe the design of Te Ara Mua – Future Streets, a mixed-methods, controlled before-after intervention study to assess the effect of retrofitting street changes at the suburb scale on multiple health, social and environmental outcomes. The study has a particular focus on identifying factors that improve walking and cycling to local destinations in low-income neighbourhoods and on reducing social and health inequities experienced by Māori (Indigenous New Zealanders) and Pacific people. Qualitative system dynamics modelling was used to develop a causal theory for the relationships between active travel, and walking and cycling infrastructure. On this basis we selected outcomes of interest. Together with the transport funder, we triangulated best evidence from the literature, transport policy makers, urban design professionals and community knowledge to develop interventions that were contextually and culturally appropriate. Using a combination of direct observation and random sample face to face surveys, we are measuring outcomes in these domains of wellbeing: road-user behaviour, changes to travel mode for short trips, physical activity, air quality, road traffic injuries, greenhouse gas emissions, and perceptions of neighbourhood social connection, safety, and walking and cycling infrastructure .

**Discussion:**

While building on previous natural experiments, Te Ara Mua - Future Streets is unique in testing an intervention designed by the research team, community and transport investors together; including a wide range of objective outcome measures; and having an equity focus. When undertaking integrated intervention studies of this kind, a careful balance is needed between epidemiological imperatives, the constraints of transport funding and implementation and community priorities, while retaining the ability to contribute new evidence for healthy, equitable transport policy.

The study was retrospectively registered as a clinical trial on 21 June 2018 in the ISCRTN registry: ISRCTN89845334 http://www.isrctn.com/ISRCTN89845334

## Background

Economic development in most cities around the world has been accompanied by a transition from human-powered to fossil fuel-powered transport. The form and function of cities have changed to accommodate motor vehicle dependency, and in many places walking and cycling have been designed out of daily lives. This transformation has had important consequences for human health [1], social and health equity [2] and future urban resilience [3]. New Zealand (NZ) cities follow this pattern: three quarters of urban trips are now undertaken in a private motor vehicle [4].

Road traffic injuries are a major cause of death, disability and health inequity in NZ, with a high rate of road traffic fatalities compared with other Organisation for Economic Co-operation and Development (OECD) countries and a total social cost of over 4 billion NZ dollars in 2017 [5]. Rates are particularly high in children and young people [6]. NZ has recently seen increases in road traffic injury deaths in the past 5 years, even taking into account population growth [7], following a 20-year decline, and despite improvements in regulation, education and vehicle technology. Vehicle-related urban air pollution also has a significant cost in early mortality and morbidity in NZ, including approximately 400 deaths a year [8].

Climate change is widely considered to be this century’s most pressing environmental and public health problem [9]. Transitioning to a low carbon urban future is one of the major challenges facing society. Making a well-planned transition is vital if we are to reap the potential economic, societal and health co-benefits of low carbon cities [10, 11]. Transport is one of the largest and fastest-growing contributors to greenhouse gas emissions. In this sector there are potentially substantial co-benefits for health and health equity associated with carbon-saving interventions [12–14].

Like climate change, obesity is attributable, in part, to the motorization and mechanization of urban lives [15]. NZ has the third highest obesity rates in the world, with 30% of adults classified as obese [16]. Built environments that discourage walking and cycling often associated with physical inactivity, obesity, and related diseases [17].

Car-dependent transport patterns in cities have other undesirable effects on the determinants of health and health equity. These include: socioeconomic, ethnic and gender inequities in access to goods, services, employment and education [2]; threats to social connection and sense of safety from crime [18]; water quality [19]; and household financial vulnerability to expected oil price rises [20]. Very few of these public health outcomes are currently included in transport decision-making.

There are many pathways between urban planning and health and these do not operate independently. Interactions between variables are complex and cyclical [21–23], requiring consideration of the complex causal theory underpinning any intervention study design.

Systematic reviews of interventions to encourage walking and cycling and reduce pedestrian injury have reported that behaviour change programmes alone are largely ineffective [24–27], but infrastructure that improves walkability, traffic calming, and proximate access to destinations including local parks for recreation can all successfully encourage walking and cycling and reduce pedestrian injury [28, 29]. The reviews conclude that there is a dearth of high quality epidemiological research assessing the effectiveness of environmental change, and outline the challenges of such research. Not only are accurate measures of outcomes difficult to achieve, but such studies also require both interdisciplinary research partnerships (including, for instance, epidemiologists, social scientists and built environment researchers), and connections between researchers, urban planning or transport agencies, and communities (*transdisciplinarity*) [21]. Similarly, the growing discipline of EcoHealth suggests that meeting goals to improve human health in the context of social and environmental determinants, environmental sustainability and equity, requires systems thinking; transdisciplinary and mixed methods research; community participation; and approaches that enable rapid translation of knowledge into action [30].

Robust community-level trials of changes to transport are challenging to design and undertake successfully, particularly when the parties involved in the research are not aligned in terms of priorities, funding, timetables and expectations in general. In most instances, natural experiments or quasi-experimental designs have been used. In the United Kingdom [31–33], Australia [34] and NZ [35] this approach has been taken to investigate the impacts on walking and/or cycling of transport agency-led interventions to improve the active transport environment. These studies have found either no, or only small, positive impacts of the interventions on active transport and physical activity in the shorter term, with greater impacts found at longer-term follow-up [32], suggesting that intermediate outcomes as well as physical activity end points need to be considered.

Common limitations of studies of infrastructure for active transport and health include small sample size (and poor generalisability), low response rates, limited follow-up, and lack of control by the researchers over the characteristics, quality or intensity of the intervention. Heterogeneity in the nature of the interventions has limited a clear understanding of optimal infrastructure. Further, there is an absence of integrated outcomes assessment or integrated cost-benefit analysis across broad public health outcomes. There is an absence of evidence about interventions that could reduce social and health inequities mediated by transport system design. Moreover, no studies in this field have objectively measured physical activity [29], despite well-known limitations with using self-reported physical activity. A recent paper on epidemiological bias in natural experiments designed to study the effect of built environment changes on physical activity [32] concluded that even the highest quality studies to date are susceptible to significant systematic error, undermining our ability to draw robust conclusions. The authors proposed study design improvements, including: better matching of control and intervention sites, more stringent adjustment of confounders, use of objective outcome measures, improved reporting of population sample and interventions, and improved measurement of individual exposures to interventions.

Building on the experience of previous natural experiment studies, and attempting to address the challenges identified in the literature, Te Ara Mua-Future Streets (Future Streets) is a *transdisciplinary* project, in other words, it aims to integrate community, policy and research knowledge and assess a range of outcomes [36, 37]. It is an area-level randomised, controlled before-after intervention study, which aims to:develop a best practice walking and cycling infrastructure intervention in a suburb with a high proportion of low income residents (measured by neighbourhood level deprivation) and a high proportion of residents experiencing inequities associated with ethnicity (particularly Māori – NZ’s indigenous peoples, and Pacific peoples);use best practice community co-design for the infrastructure intervention, triangulating community knowledge with high quality evidence;measure behavioural, perceptual and integrated public health outcomes from the intervention; andmodel the costs and benefits of more widespread intervention implementation.

## Methods

The intervention design was informed by cognitive psychology concepts of affordance, (where the road environment allows for a set of road-user behaviours) [38] and schema and scripts (where people have a mental map of what roads look like and how they work, as well as a set of expected behaviours, reinforced or disrupted by environmental design) [39]. These concepts are incorporated into an approach to road design known as “Self-Explaining Roads” (SER) [40, 41]. The SER approach focuses on three principles: hierarchical road function (for arterial roads, collector roads and local streets); consistency of mass and speed on each road type; and predictable behaviour through consistent design [42]. An earlier SER intervention study demonstrated its effectiveness for reducing motor vehicle speeds and road traffic crashes, as well as changing the way pedestrians used the streets [40, 43].

To achieve our aim of community co-design of an intervention that reduces health inequities, we incorporated a significant community engagement phase and Māori cultural landscape design principles (Te Aranga principles [44, 45]). Māori, the indigenous peoples of NZ, experience significant inequities for many of the health outcomes relating to transport. In addition, Māori have specific rights under their treaty with the Crown (Te Tiriti o Waitangi [46]) for the protection of their wellbeing and equity of outcomes. Low-income and Pacific peoples in NZ also experience significant inequities relating to transport and urban design. We sought to understand whether community co-design with these groups, prioritising Māori, would help to address inequities.

We drew on prior ecological causal theories of transport walking and cycling [13, 22, 23, 47–49] to develop a complex, dynamic causal theory, in the form of a Causal Loop Diagram (CLD) [50], of the relationships between infrastructure for walking and cycling and a range of outcomes (Fig. 1). The multiple cyclical feedback mechanisms described in the CLD will vary in strength and relevance by context.

**Fig. 1 Fig1:**
[figure not shown]
Dynamic causal theory linking built environment, local walking and cycling and outcomes for wellbeing, expressed as a Causal Loop Diagram (CLD). Variables in green are being assessed during the Future Streets study. Arrows with positive signs (+) indicate that a change in the arrow-tail variable leads to a corresponding change in the arrow-head variable. Arrows with a negative sign (−) indicate that a change in the arrow-tail variable leads to an inverse change in the arrow-head variable. R – Reinforcing loop, the result of which is an amplification of the initial pattern of behaviour. – Balancing loop, the result of which is a dampening of the initial pattern of behaviour

### Research and implementation partnership

The project was developed in partnership with Auckland Transport, the regional transport planning and investments authority, who committed to funding the intervention construction. Project implementation has been guided by 1) a steering group made up of research team and transport agency representatives and 2) a local stakeholder advisory group, led by the local community board, with membership including Mana whenua (Māori tribes with local authority over the Māngere area), community leaders, local primary schools, urban Māori, local Police and health promotion workers. These two sets of partnerships have been active throughout the project. An in-depth discussion of researcher and transport agency relationships is reported elsewhere [51].

### Setting

The project is based in Auckland, the largest and fastest growing city in NZ, with a population of 1.5 million. A program of motorway development and low-density urban growth in Auckland has led to exponential growth in car ownership and use, with a collapse in use of public transport and bicycling as modes of transport [52, 53]. In the most recent national census, private motor vehicles were used for 85% of commutes in Auckland, with public transport, walking and bicycling used less frequently (9, 5, and 1%, respectively) [4].

In 2013, the following criteria were used to choose intervention and control study neighbourhoods, of approximately 1400 households and 6500 people in each neighbourhood:
**Primary characteristics**
Potential for accessibility to local destinations, drawing on existing indices of accessibility and walkability at a census area level [54, 55]High levels of social and economic deprivation as measured by the census-based neighbourhood deprivation scale (NZDep2006 Index of Deprivation [56])A high proportion of Māori and Pacific residentsHigher than average rates of road traffic injury
**Secondary characteristics**
5.Based on natural ‘community’ boundaries, without major dividers such as a motorway6.Alignment with the region’s cycle network planning, so that the intervention area is likely to eventually connect to a wider network

Two neighbourhoods within the larger suburb of Māngere were selected by the steering committee in 2013. For the purposes of the project, these areas were named ‘Māngere Central’ and ‘Māngere East’. These areas are shown in Fig. 2. At the time of selection, the two areas had comparable demographic profiles and street layouts but are separated by a motorway. Auckland Transport had identified no major infrastructure projects planned in either area during the study period.

**Fig. 2 Fig2:**
[figure not shown]
Map of intervention and control areas. Intervention area is labelled “Central Māngere”, control area is labelled “East Māngere”. (Map credit: [name], Massey University 2013, with permission)

A computerised random number generator was used to randomise the two areas to intervention and control. Since there were only two areas, random allocation could not serve its usual purpose (to distribute evenly known and unknown confounding factors), rather it ensured the intervention area was not chosen because it was more in need of improvement or more receptive to change.

Intervention and control areas were both to receive ‘business-as-usual’ transport initiatives (including other minor infrastructure improvements, educational and promotional activities) during the project. These included active transport encouragement or organisational travel planning that might be occurring at a regional level. Any differences in delivery of such initiatives across the study sites are being documented.

### Intervention design

A detailed description of the process and outcomes of the participatory intervention design has been reported elsewhere [57]. Contextual transport and place information from community groups and Māori iwi (extended kinship group) with local area authority was triangulated with baseline vehicle counts and speeds, pedestrian and cyclist counts, and video movements of pedestrians and cyclists across the intervention and control areas, to identify most used routes and crossings, as well as places of high conflict between road users. A clear road hierarchy map was developed from these data, differentiating three types of road: arterial roads, collector roads, and local streets.

These multiple datasets were used to develop a set of guiding design principles that prioritised the issues identified through the participatory process. Initial draft infrastructure intervention designs were then developed by Auckland Transport, including a range of infrastructure changes to reallocate road space from vehicles to pedestrians and cyclists; improve street crossing safety and convenience; improve the safety of routes through parks; and landscaping to reflect indigenous culture and history.

An iterative process of engagement and revision was used to develop the final designs, examples of which are shown in Fig. 3.

### Outcome measures

Measures of hypothesized influences on, and outcomes of, walking and cycling are described below. The outcome measures are listed in Table 1. Short-term follow-up occurs 6–14 months following intervention completion, and longer-term follow-up will occur 2.5–3 years post intervention. Outcome measures include physical health outcomes (e.g. diabetes, injury), risk factors (e.g. physical inactivity and air pollution), social and environmental health outcomes (e.g. social connection), with a mixture of individual and area-level measures. On the basis of travel behaviour and risk factors we will model longer-term health outcomes that cannot feasibly be measured in a study of this duration. Follow-up measures are matched by month to baseline, to control for seasonal effects. Daily weather data will be included as a control variable in analyses.

**Table 1 Tab1:** Summary of Future Streets outcome measures and their timing

	2014	2015	2016	2017	2018	2019	2020	2021
*Intervention construction*		*X*	*X*					
Objective physical activity	X						X	
Road traffic injury	X					X		
Air quality measures	X					X		
Diabetes risk	X			X		X		
Vehicle speeds	X			X	X	X		
Road user counts	X			X	X	X		
Video measure of road user behaviour	X			X	X	X		
Face-to-face survey	X			X		X		
Climate pollution modelling	X			X			X	
Qualitative interviews/focus groups	X				X			
Retrospective analysis of safety and security		X						X
Health outcome and cost-benefit modelling					X		X	X

Because of the wide range of study outcomes and the paucity of previous intervention research in this area, calculating a sample size for the outcome measures was not straightforward. We were particularly interested in the objective measurement of physical activity, as a novel addition to the existing literature, and calculated sample size based on changes in steps measured by pedometry. Repeated measures sample size was based on the ability to detect a 1000 steps per day change in physical activity measured by pedometer, supported by previous research [38], with the expectation of 30% loss to follow up for survey participants. Based on these calculations, we aimed to recruit 360 child and 720 adult participants (to allow age group sub-analysis in the adult group) in each area to the survey and pedometer measures. This allowed for 80% power to detect change with a significance level of *p* < 0.05.

### Random sample face-to-face resident survey

A longitudinal random sample survey of children and adults, combined with pedometer measures of physical activity, is one of the core components of the study. We visited all houses in the case and control areas in 2014 to enumerate households so that we could sample participants by person and avoid household cluster effects. Individual adults and children were randomly recruited across the two areas using a pre-determined probability of selection, different for adults and children, based on the latest census population data and our expected response rate. Face to face surveys were conducted with the recruited participants (adults and parent-child pairs), using their language of choice (Samoan, Tongan, English). All households with a participant in 2014 were revisited in 2017 and those who took part in the 2014 survey were invited to repeat the survey. A replenishment sampling strategy was used to replace participants who were lost to follow-up, by recruiting new participants from the original address, using the same overall individual selection probability as in the sample of 2014. This sampling strategy was designed to retain as much of a longitudinal sample as possible, despite high residential mobility in Māngere. The replenishment sample at short-term follow-up will become a longitudinal sample at longer-term follow-up. Replenishment samples are useful [58] as they may increase power in analysis; enable exploration of the randomness of loss to follow-up, assess changes in the population, and will facilitate recruitment of a new group of children to account for aging. In 2019 this strategy will be repeated.

The survey contains the following elements:**Demographics**: age groups; ethnicity, sex, duration of residence in Māngere, marital status, highest academic qualification, current employment situation; whether they were forced to buy cheaper food or visit a foodbank in the last 12 months (and if so, how frequently) [59]; the number of driveable motor vehicles and usable bicycles at the dwelling; individuals in the household holding a NZ drivers licence; whether the dwelling is rented/owned; combined household income before tax in last 12 months; and household composition (children, youth, adults). Questions were adapted where possible from the NZ Health Survey [60] and the 2006 Census [61].**Active transport**: items from the iConnect survey [62, 63] were used to enumerate trips to and from destinations across seven categories of trip purpose (e.g. work, study, or social activities). For each category, participants were asked to report the total number of journeys in the previous 7 days, average trip time, and main transport mode used.**Leisure-time physical activity**: items from the International Physical Activity Questionnaire-Long Form (IPAQ-LF) [64], previously demonstrated to be comprehensive, reliable and valid, were used with the previous 7-days as the reference period. The IPAQ-LF provides separate estimates of physical activity in specific domains.**Sitting time:** assessed using the IPAQ-LF. Sitting items ask respondents to report usual duration of sitting while at work, at home, while doing course work and during leisure time in the last 7days.**Neighbourhood perceptions and social wellbeing:** individual items on neighbourhood perceptions were drawn from the validated, reliable Neighbourhood Environment Walkability Scale-Abbreviated version (NEWS-A) [65]. Perceived ease of cycling in the neighbourhood was assessed using an item from the Australian Cycling Connecting Communities Study, in which this item was associated with residents wanting to ride more, and was predictive of past cycling in previous studies [66, 67]. Perceived neighbourhood safety, social cohesion, and social connection were assessed using items from the Ranui Action Project Survey, successfully used with adults and children from ethnically diverse low-income neighbourhoods [68], and to understand children’s independent mobility in Auckland [69].**Self-reported road traffic injuries (RTIs):** questions from the World Health Organization (WHO) guidelines [70] for conducting community surveys on injuries have been adapted to elicit self-reported RTIs as well as non-injury collisions and crashes for all modes of transport in the past year, counting injuries which prevented carrying out normal daily activities for at least 1 day or for which they had any type of treatment. For each injury, information was collected on health service utilisation, transport mode at the time of injury, other vehicles involved, date, and location.**Physical abilities**: questions about hearing, vision, mobility, and wheelchair or mobility scooter use are based on the 2006 NZ Disability Survey [71].

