### Statistical analysis

Data will be analysed according to area, the scale of measurement, distributional assumptions and sampling structure, accounting for the longitudinal sample as well as the cross-sectional sample. We will use separate generalised linear mixed models, adjusting for repeated measurements. If the replenishment sample is comparable to the participants lost to follow-up, we will use both sets of data in combined models, testing the sensitivity of results to our assumptions of similarity. Potential explanatory model terms and covariates in the statistical analysis will be identified a priori from our causal theory and by the use of Directed Acyclic Graphs. Because this is a complex, area-level intervention, with social components, residents living in the intervention area will be considered “exposed”, while residents living in the control area will be considered “unexposed”. In our primary analysis, we will consider exposure to be homogenous across the areas. Secondarily, we will be exploring more nuanced approaches to individual-level intervention exposure, including distance between residential address and the nearest intervention treatment.

Outcome variables to be included in analyses include: mean, median and 85% vehicle speeds, and vehicle counts by road type; changes in the mean numbers of pedestrians and cyclists seen in video data; mean reported minutes walked or cycled; mean trips walked or cycled; median weekly minutes of reported physical activity - total, recreational and transport; mean steps per day as measured by pedometer; mean perceived and objective sense of security and neighbourhood perceptions scores; self-reported and routinely recorded injuries by mode and by injury severity; changes in mean NO_2_ on different route types; and changes in mean HbA1c. Some identical questions between child and adult surveys will be analysed together, though we will also analyse child and adult survey data separately, stratify survey analyses by sex, adult age group, income, and ethnicity (including separate Pacific ethnicities), and explore differences by mobility.

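### Sampling by person does not avoid household clustering: about half of participants are expected to share a household, and no household term is named in the analysis

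*Protocol article*

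**What the plan says.** The section on the random sample face-to-face resident survey gives the purpose of enumeration as to "enumerate households so that we could sample participants by person and avoid household cluster effects". Adults and children were then recruited "using a pre-determined probability of selection, different for adults and children". No limit of one participant per household is stated. The same section continues: "Face to face surveys were conducted with the recruited participants (adults and parent-child pairs"). People lost to follow-up are replaced by new participants at the same address.

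Under Setting, the areas are described as "of approximately 1400 households and 6500 people in each neighbourhood". Under Outcome measures, "we aimed to recruit 360 child and 720 adult participants (to allow age group sub-analysis in the adult group) in each area".

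Under Statistical analysis: "We will use separate generalised linear mixed models, adjusting for repeated measurements". That section also says that the analysis will respect how the sample was drawn, and goes on to name the longitudinal and cross-sectional samples. It adds: "Some identical questions between child and adult surveys will be analysed together". Child and adult data will be analysed separately as well. The Discussion plans one analysis that assumes independence and one that explores its violation, in a paragraph about area-level clusters. Neither section mentions households.

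**The concern.** Drawing individuals removes household clustering only if no two participants live together. Here about one resident in six is sought, in households averaging more than four people, so shared households are to be expected. Members share what the survey itself records at household level, such as vehicles, bicycles, income and tenure, as well as the street.

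Because the article states that the design has dealt with household effects, an analyst following it has no reason to add a household term. Each household lies wholly within one area, so positive correlation between members tested in the same wave makes the standard error of the area comparison too small if it is ignored. This is separate from the problem of having only two areas, which the article acknowledges.

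**Working it through.** **The plan's own figure.** The recruitment target cannot be reproduced from the article, because no SD is given. With an assumed SD of change of 4000 steps, a two-sided 5% test and 80% power, n = 2 × (1.960 + 0.842)² × (4000/1000)² ≈ 252 per area, and 252/0.70 = 360, the child target. That match contains no allowance for household clustering, but it rests on the assumed SD and proves nothing by itself.

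**Expected overlap.** Inputs from Setting and Outcome measures: 1400 households, 6500 people, 360 + 720 = 1080 participants.

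- Mean household size s = 6500/1400 = 4.64. Sampling fraction f = 1080/6500 = 0.166.
- Near-equal household sizes: share with a co-participant = 1 − (1 − f)^(s−1) = 1 − 0.834^3.64 ≈ 0.48. Size-weighted number of participants per household m = 1 + f(s − 1) ≈ 1.61.
- Simulation (200 draws each; near-equal, Poisson-like and over-dispersed household sizes):

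| Sample | Share with a co-participant | m |
|---|---|---|
| 1080 pooled | 48–58% | 1.61–1.98 |
| 720 adults | 35–45% | 1.41–1.64 |
| 360 children | 19–26% | 1.20–1.32 |

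The fewest multi-participant households in any simulated draw of 1080 was 220. All draws were from the full 6500, because the article does not give the adult-child split. If there were 4000 adults (assumption) in near-equal households, f = 0.18, s = 2.86, and the adult share would be 1 − 0.82^1.86 ≈ 31%. Parent-child pairs are not built into these draws. Data made up wholly of pairs would have m = 2.

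**Single-wave comparison.** Design effect = 1 + (m − 1) × ICC; true SE / naive SE = √(design effect). The ICC is not given; 0.1–0.3 is assumed.

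| Sample | Design effect | True SE / naive SE |
|---|---|---|
| Pooled | 1.06–1.29 | 1.03–1.14 |
| Adults alone | 1.04–1.19 | 1.02–1.09 |
| Children alone | 1.02–1.10 | 1.01–1.05 |

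For pooled data the naive SE is too small by 1 − 1/1.03 ≈ 3% up to 1 − 1/1.14 ≈ 12%. A nominal 5% test then runs at about 5.7–8.5%. At ICC 0.05 the SE effect is only about 1–2.5%.

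**Before-after comparison.** Simulation of 1080 per area (Poisson-like household sizes, 3000 runs), analysed as if people were independent:

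| Situation | SE ratio, ICC 0.1 / 0.3 | Rejection at nominal 5% |
|---|---|---|
| Single wave | 1.04 / 1.11 | 5.7% / 7.7% |
| Change in retained people, stable household effect | 0.99 / 1.00 | 5.1% / 5.1% |
| Change in retained people, changes correlated within household | 1.02 / 1.11 | 5.7% / 7.6% |
| Everyone replaced one for one at the same address, stable household effect | 0.95 / 0.83 | 3.9% / 1.9% |

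The last row agrees with theory: the household effect cancels, so the ratio is √(1 − ICC) = 0.95 and 0.84. Full replacement is an extreme; the real sample mixes the last three rows.

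**The case against.** The strongest objection concerns the estimand. The sample size is for change in steps, and the models handle repeated measurements. A stable household effect drops out of each person's own change, so the cross-sectional design effect does not describe the analysis for which the study was powered. This stands. So does the point that replacement at the same address can make naive intervals too wide, and that a household random intercept alone would leave the area-by-time standard error for retained people unchanged.

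A reader might infer that clustering is guaranteed, that every standard error is too small, and that power falls to some stated figure below 80%. The documents do not support this. With 1080 participants and 1400 households, one per household was arithmetically possible; overlap follows because selection was by individual probability with no limit stated. One per household would also have needed a participant in 77% of homes (1080/1400). The article does not say whether the parent in a pair gives own outcome data or counts among the 720 adults. No ICC of change is given from which a power loss could be computed.

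It can also be said that random-effect levels belong in an analysis plan that is not shown, and that the article promises to respect the sampling structure and to explore violated independence. The absence of a household term would not be a finding by itself. But the article makes a positive statement that its design does not bear out, its general wording goes on to the longitudinal and cross-sectional samples, and its independence analysis is discussed for areas.

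**Conclusion.** The statement that household cluster effects are avoided is not supported by the article's own numbers and procedures. Under individual-probability selection with no household limit, about half of participants are expected to share a household (48–58% across assumed household-size distributions; 35–45% for adults alone, somewhat fewer if there are many fewer adults than 6500).

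The consequence is miscalibration of modest size that differs by analysis:

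- **Cross-sectional and pooled child-adult comparisons:** naive standard errors about 3–12% too small at an assumed ICC of 0.1–0.3, and less for adults or children alone.
- **Change in retained participants:** almost no error if household effects are stable; an error of similar size to the single-wave one only if changes are correlated within households.
- **Same-address replacements:** naive intervals may be too wide.

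This warrants correction because the claim steers the analyst away from a cheap safeguard. It does not show that the planned power is missed.

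**What to change.** Delete the words on avoiding household cluster effects, or qualify them to say that people were sampled individually and some households contribute more than one participant.

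In all survey and pedometer models, account for household (address) by household-clustered robust standard errors, or by household plus household-by-wave random effects alongside the person-level term. Keep one address identifier across waves, so that a lost participant and the replacement are linked. This matters most for pooled child-adult analyses and for models combining the longitudinal and replenishment samples.

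Report the number of participants per household by area and wave, and say whether the parent in a pair contributes own outcome data and counts towards the adult target.

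Cost: a little more analysis work and usually slightly wider intervals. No new data are needed, since households were enumerated and revisited by address.
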